#### Plans for collection, laboratory evaluation and storage of biological specimens for genetic or molecular analysis in this trial/future use {33}

No biological specimens are being collected.

## Statistical methods

### Statistical methods for primary and secondary outcomes {20a}

All data analysis will be in accordance with the Consolidating Standards of Reporting Trials (CONSORT) [48, 49] guidelines and the primary statistical analyses will be conducted on a modified intention-to-treat basis including all participants contributing at least one quality of life measurement. Baseline variables to be explored are shown (Table 1). Patient-reported outcome scores based on standardised questionnaires will be calculated based on the developers’ scoring manuals and missing and erroneous items will be handled according to these manuals. Continuous measures will be presented as means and standard deviations or medians and ranges depending on their distribution. Categorical data will be presented as frequencies and proportions. A full statistical analysis plan will be developed and agreed by the Trial Steering Committee (TSC) prior to undertaking any analyses of the trial data.

#### Primary outcome analysis

The primary endpoint in this study is quality-adjusted life years which will be calculated using EQ-5D-5L data collected 4-monthly and survival data. The primary statistical analyses between the randomised groups will be conducted on a modified intention-to-treat basis including all participants contributing at least one quality of life measurement. Utility scores will be estimated from the EQ-5D-5L using the NICE-recommended approach at the time of analysis and these will be used to compute QALYs experienced over the follow-up period using the area under the curve approach. Depending on the distribution of the observed QALYs data, appropriate regression techniques will be applied. If normally distributed, the mean differences in QALYs between treatment arms with 95% confidence intervals will be calculated using multivariate linear regression models. Otherwise, the shape of the distribution will be considered to inform the choice of alternative, suitable regression models (including non-parametric models) for this outcome. All models will adjust for baseline EQ-5D-5L scores.

#### Secondary outcome analysis

Survival will be assessed using Kaplan–Meier curves and a Cox proportional hazard model analysis. Hospital-free days will be studied using appropriate regression models—such as the negative binomial model with offset for the duration of follow-up—based on the distribution of the data. Appropriate repeated measures regression models for patient-reported outcome scores will be chosen based on the distribution of each outcome.

A detailed statistical analysis plan will be developed for the approval of the TSC prior to analysis. Any deviations from the approved plan will be described and justified to the TSC for their approval.

#### Economic data analysis

The trial includes a formal economic evaluation comparing the costs and outcomes of the ‘preparing for responsive management’ and ‘preparing for renal dialysis’ arms of the trial from the perspectives of (a) the NHS and PSS and (b) society, including patients and close persons, from the point of randomisation (i) up to an estimated average of 3 years based on trial data alone and (ii) to death based on trial data combined with decision modelling. Economic evaluation will take the form of (i) cost-effectiveness analysis using QALYs generated using EQ-5D-5L, (ii) cost-effectiveness analysis using years of full/sufficient capability equivalence gained using ICECAP, (iii) cost consequences analysis including all costs and outcomes presented in disaggregated format. QALYs will be estimated from EQ-5D-5L scores as specified in the “Primary outcome analysis”.

Valuations will be assigned to capability outcomes based on published UK population tariffs at the end of the study [27]. All resource use will be valued using unit costs derived from national sources where available.

The economic data analysis will be conducted on an intention-to-treat basis using an incremental approach. Mean total costs and outcomes will be calculated across all patients and incremental cost-effectiveness ratios for the trial arms will be estimated to produce an incremental cost per QALY gained/cost per year of full/sufficient capability equivalent gained from both health and societal perspectives. Missing cost and outcome data will be imputed using appropriate methods, if appropriate [50]. To avoid bias, imbalances in baseline utility/capability/costs between the groups will be controlled for [51]. Discounting will be applied at the NICE-recommended rate of 3.5% [52]. Given the multicentre nature of this study, it may be appropriate to use hierarchical modelling techniques (with explanatory variables stratified into patient and centre levels).

It is anticipated that significant numbers of patients may not have died by the end of the trial and so modelling will need to be used to extrapolate beyond the trial, to capture costs and impacts for the remaining lifetime. Markov models will be developed to simulate the clinical pathways of patients with advanced CKD for both economic outcomes. Markov models are appropriate as they can represent situations where patients change from one state to another (for example, the shift to dialysis) as well as experiencing recurrent states (such as remaining on dialysis) over long periods of time. The models will be structured such that clinical pathways are based on the arms of the trial. Transition probabilities, costs and outcome information (in terms of both health-related QoL and capability wellbeing) will be taken primarily from the trial, but will be supplemented with information from routine datasets and published data, where necessary; time-dependent probabilities will be used as in other Markov models of advanced CKD [53]. Time intervals for transitions between states will be based on the four-monthly follow-up period within the trial.

Uncertainty will be explored using deterministic (trial and model) and probabilistic (model only) sensitivity analyses. Deterministic sensitivity analysis will focus particularly on those issues where it has been necessary to make assumptions about resource use and/or cost or where particular issues have been encountered. Probabilistic sensitivity analysis will be used to estimate the joint effect of uncertainty in the model parameters. Results will be presented as the incremental cost-effectiveness ratio and using cost-effectiveness acceptability curves to show the probability that the results fall below given cost-effectiveness thresholds. Results will be compared to the NICE recommended cost per QALY threshold at the time of the completion of the study [52] Thresholds for the ICECAP measures will be applied based on deliberative research for ICECAP-A [54].

#### QRI and qualitative data analysis

Analysis of QRI data.

Screening log data will be analysed and summarised descriptively. Interviews will be audio-recorded using digital encrypted recorders, transcribed verbatim and edited to ensure anonymity and managed using NVivo software (QRS International). Transcripts will be analysed thematically using constant comparative approaches adopted from Grounded Theory [55]. Audio-recorded recruitment appointments will be subjected to content, thematic and novel analytical approaches, including targeted conversation analysis [56]. Standard approaches to enhancing rigour, such as double-coding and seeking out ‘negative cases’, will be employed throughout the conduct of the QRI. Descriptive accounts of each qualitative data source will be written and iteratively updated as data collection and analysis progress, enabling ongoing discussion and joint interpretation of data amongst the QRI team. A detailed description of approaches to analysing and triangulating QRI data is published elsewhere [46].

Analysis of interviews investigating acceptability and compliance issues.

Interviews conducted with HCPs and trial participants/relatives will be analysed thematically, as reported above, with the same approaches to safeguarding rigour employed throughout (e.g. double coding, production of iterative descriptive accounts, and regular discussion of evolving findings in team meetings). Repeat interviews for trial participants will be analysed and written up as individual case studies, with cross case-comparisons informing overarching findings from this group as data collection/analysis progresses. We will code and write up findings from each stakeholder group (i.e. patients, relatives, HCPs) separately in the early stages of analysis, with regular cross-checking of themes emerging from each group to inform new lines of enquiry and promote interrogation of the data through different lenses. With time, findings from each group will be triangulated to inform a single report.

### Interim analyses {21b}

No formal interim statistical analyses of the principal outcome measure are planned. However, mortality rates will be reported routinely to the DMC by arm (unblinded). The DMC will consider a recommendation to discontinue recruitment, in all patients or in selected subgroups, only if the result is likely to convince a broad range of clinicians, including those supporting the trial and the general clinical community.

### Methods for additional analyses (e.g. subgroup analyses) {20b}

We will conduct pre-planned subgroup analyses to investigate any differential effects according to a number of factors. These will be done by introducing appropriate interaction terms in the regression models. We will carry out these analyses by age at baseline (65–79 years vs ≥ 80 years) and rate of kidney function decline in the 12 months pre-baseline (≤ 5 ml/min/1.73 m^2^ vs > 5 ml/min/1.73 m^2^). In the group aged 80 years and over we will also stratify according to comorbidity scores at baseline (< 2 vs ≥ 2) and WHO performance status at baseline (< 3 vs ≥ 3).

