Based on summary statistics from the observed data and visual inspection of the histogram, we simulated datasets of 1,000,000 observations for comparator groups using the SKBIM command in STATA [40]. This command allows the user to simulate a bimodal distribution while specifying different characteristics of the distribution including means, standard deviations, skewness and kurtosis (for the comparator group the simulated dataset was generated with this command: skbim (0.5 0.359 0.096 2.413 2.413 0.154 1 1000000 123 0.804 2.492 0 3)). To simulate the distribution of QALYs in the intervention group, we assumed the same distribution as the comparator group, but shifted the two means by 0.345 QALYs to reflect a clinically meaningful difference we wanted to be able to detect. Simulated values greater than 3 were discarded.

Sample size calculations involved re-sampling (1000 iterations) with varying sample sizes from these simulated distributions of continuous QALY scores and performing Mann Whitney tests. To allow for possible cross over, we selected our intervention group samples by taking 95% of our sample from the intervention distribution and 5% from the comparator distribution. The same process was used to identify the comparator group sample.

Having 230 patients per group allows detection of a difference between the pathways of 0.345 QALYs with 90% power (2-sided a = 0.05). Death is not a censoring event (utility becomes and remains 0) so loss-to-follow-up should not exceed 10%. Allowing for loss-to-follow-up increased the total sample size to 512.

Following the COVID-19 pandemic, recruitment rates have improved but are still generally tracking below predicted. Following discussions with the Trial Steering Committee (TSC), Patient Advisory Group (PAG) and funder, the Trial Management Group (TMG) has agreed to extend recruitment to ensure 85% power is achieved. Using the original sample size simulations and associated assumptions, this reduces the target sample size from 512 to 446 participants.

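### The planned interaction test for rate of kidney function decline splits a continuous modifier at 5 ml/min/1.73 m², which discards a third to a half of its information if modification is roughly linear

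*Protocol article*

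**What the plan says.** The section on additional analyses {20b} announces the subgroup work: "We will conduct pre-planned subgroup analyses to investigate any differential effects according to a number of factors". The method is an interaction test: "These will be done by introducing appropriate interaction terms in the regression models". For kidney function the factor is "rate of kidney function decline in the 12 months pre-baseline", and its form is fixed as two groups, ≤ 5 versus > 5 ml/min/1.73 m². No continuous or non-linear analysis of this factor is mentioned.

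The other splits in that section have an anchor elsewhere in the article. Age 65–79 versus 80 and over is the minimisation factor (Sequence generation {16a}). Comorbidity score 2, WHO performance status 3 and age 80 are eligibility thresholds (Inclusion criteria). A decline of 5 appears in neither place.

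All power statements concern the main effect: "Having 230 patients per group allows detection of a difference between the pathways of 0.345 QALYs with 90% power", later revised so that "this reduces the target sample size from 512 to 446 participants" at 85% power. No interaction effect or interaction power is given.

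**The concern.** Rate of decline is continuous. The two-group form treats a fall of 0 and a fall of 5 as the same, and a fall of 4.9 and a fall of 5.1 as different. The comparator section describes dialysis as starting if kidney function falls, so it is plausible that the pathways separate sooner in faster decliners and that any modification is graded. In that case a two-group contrast is an inefficient test.

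The Discussion counts the planned subgroup analyses as part of the trial's answer to the criticism that trials report only average effects. The trial is sized for the main effect, so information on interactions is already scarce. Discarding part of it makes it more likely that a real gradient is reported as no differential effect. The result also depends on how many participants happen to lie above 5.

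**Working it through.** **1. The plan's own figures (Sample size {14}).** Inflation for loss: 460 / (1 − 0.10) = 511.1, or 512 when rounded up to an even total. At the revised target, 446 × 0.90 = 401 analysed, about 201 per group.

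The simulated comparator distribution is given as "skbim (0.5 0.359 0.096 2.413 2.413 0.154 1 1000000 123 0.804 2.492 0 3" and "Simulated values greater than 3 were discarded". I read it as a 50:50 mixture with means 0.359 and 2.413, and take 0.096 and 0.154 as variances (an assumption). With a shift of 0.345, 5% crossover each way and Mann-Whitney tests, power is about 88 to 89% at 230 per group (stated 90%) and about 83% at 201 per group (stated 85%). The plan's figures are therefore reproduced closely. The reading matters: taken as SDs, the same inputs give power near 100%, and truncating at 0 as well gives about 60%.

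Overall SD under the variance reading: √[(0.096 + 0.154)/2 + ((2.413 − 0.359)/2)²] = 1.09, and about 1.05 after values above 3 are discarded. I use 1.05.

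**2. Information kept by a split.** For a normal modifier with linear modification and a share p above the cut, the fraction kept is E = φ(z)² / [p(1 − p)], where z is the normal quantile at the cut.

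| Share above 5 (assumed) | E |
|---|---|
| 50% | 0.64 |
| 35% | 0.60 |
| 20% | 0.49 |
| 10% | 0.34 |

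**3. Power in assumed scenarios.** Let b be the change in treatment effect (QALY) per SD of decline. With 1:1 allocation the interaction has standard error 2σ/√n, so the non-centrality is λ = b√n/(2σ) for the continuous test and λ√E for the split test. With n = 401 and σ = 1.05, b = 0.20 gives λ = 0.20 × 20.02 / 2.10 = 1.91. Two-sided 5% power:

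| b | Continuous | Split 50/50 | Split 65/35 | Split 80/20 | Loss (points) |
|---|---|---|---|---|---|
| 0.05 | 7.6% | 6.7% | 6.6% | 6.3% | about 1 |
| 0.10 | 15.9% | 11.8% | 11.5% | 10.2% | 4 to 6 |
| 0.20 | 47.9% | 33.1% | 31.6% | 26.6% | 15 to 21 |
| 0.25 | 66.4% | 47.7% | 45.7% | 38.5% | 19 to 28 |
| 0.345 | 90.8% | 74.7% | 72.4% | 63.4% | 16 to 27 |

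A simulation of 1,500 trials per scenario (n = 401, two-mode QALYs with overall SD about 1.03, linear model with product term) gave losses of 15 to 31 points for b from 0.20 to 0.345 with normal decline, and 13 to 23 points with right-skewed decline (gamma, shape 2). The calculation takes QALYs as the outcome and makes no allowance for adjustment for baseline EQ-5D-5L.

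**4. When the true shape is not linear.** Efficiency is the squared correlation of the true effect shape with each coding. For an assumed gamma decline with mean 4 and SD 3:

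| True shape | Linear term | Split at 5 |
|---|---|---|
| Linear | 1.00 | 0.64 |
| Step at 4 | 0.60 | 0.61 |
| Step at 5 | 0.64 | 1.00 |
| Step at 6 | 0.64 | 0.64 |
| Sigmoid at 5, scale 0.5 | 0.78 | 0.91 |

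So the linear term loses to the split for a step or steep sigmoid at 5, and is no better for steps at 4 or 6.

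**The case against.** This is a condensed article. The full protocol is a supplement that is not shown, and a full analysis plan is promised before analysis. A reader might infer that the split has no justification at all. The documents do not support that: they show only that this article gives none. What stands is that the two-group form is a stated method, and a rationale elsewhere would not restore the lost information if modification is linear.

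A reader might also infer that this trial loses some 15 to 30 points of power. That range needs strong modification. At 0.20 QALY per SD the treatment effect differs by 0.20 × 2.56 = 0.51 QALY between the 10th and 90th percentiles of decline, and at 0.345 per SD by 0.88. Both exceed the trial's whole target difference of 0.345. With weak modification both tests have little power and the choice hardly matters. This objection stands, and it rules out a single headline figure.

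Nor does earlier separation of the pathways imply a straight line. Time to separation would vary roughly as the inverse of the rate and be limited by follow-up, so the effect could be flat at slow decline and level off at fast decline. This also stands, and is the reason for a non-linearity check.

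Finally, the slope rests on routine blood tests, and eligibility requires as few as one earlier confirmatory reading. Individual slopes may be noisy, and outliers can have leverage in a linear interaction. That is a real, modest cost of the continuous form.

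**Conclusion.** The point holds as a minor one. The article fixes the decline interaction as a two-group contrast at a value it does not tie to randomisation or eligibility. If modification is roughly linear and decline roughly normal, that form keeps between about half and two-thirds of the interaction information for shares above 5 between 20% and 50%, and less at more extreme shares.

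The loss in power is scenario-dependent: about 1 to 6 points for 0.05 to 0.10 QALY per SD and about 15 to 30 points for 0.20 to 0.345 per SD, at about 401 analysed. It is not an estimate for this trial. It would also be too strong to infer that the continuous test loses its advantage only for a step at exactly 5, since nearby steps remove it and a steep sigmoid at 5 reverses it.

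This is one pre-planned secondary analysis, and the primary comparison is not affected.

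**What to change.** In {20b} and the analysis plan, make treatment × continuous rate of decline (per 1 ml/min/1.73 m² over the 12 months before baseline) the pre-specified interaction test. Add one pre-stated check of non-linearity, for example a 3-knot restricted cubic spline. Report the treatment difference with its 95% CI at chosen percentiles of decline, such as the 10th, 50th and 90th. Keep ≤ 5 versus > 5 as a secondary or descriptive analysis, which also covers a step near 5, and state the reason for that value. Leave the age grouping as it is.

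The cost is some wording and one further model. No extra data should be needed, because a rate must be calculated before anyone can be placed in either group. The downsides are small: a functional form must be assumed, the result is less simple to present, and the analysis plan should say how noisy or outlying slopes will be handled.

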### Methods in analysis to handle protocol non-adherence and any statistical methods to handle missing data {20c}

Where missing data exist, the frequency of missing data will be indicated and if the amount of missing data differs substantially between treatment groups (> 10%) potential reasons will be explored. Sensitivity analyses will be conducted (including the use of multiple imputation methods where assumptions are met) to examine the influence of missing data on the key trial findings.

### Plans to give access to the full protocol, participant-level data and statistical code {31c}

The full protocol is available as a supplement. External groups will be able to apply to the trial management group to request access to anonymised participant-level data, as permitted by the data sharing agreements for data that has been provided through linkage.

## Oversight and monitoring

### Composition of the coordinating centre and trial steering committee {5d}

The study is supervised by a TMG consisting of grant holders and other relevant trial delivery staff. A core delivery team at the coordinating centre, consisting of chief investigator, trial manager, trial administrator and lead research nurse, meet monthly. The full TMG meets 6–12 monthly. A TSC oversees the progress of the trial and comprises of an independent chair and five other independent members, including a public and patient involvement (PPI) representative and the CI. A PAG also oversees the progress of the trial and advises on elements of trial design and conduct from the patient and public perspective. The chair of the PAG also sits on the TMG and the TSC has a PPI co-chair. The Sponsor is responsible for overall oversight of the trial.

### Composition of the data monitoring committee, its role and reporting structure {21a}

A DMC monitors accumulating trial data for quality, completeness and patient safety and comprises of an independent chair and at least two other independent members. The CI, trial manager and senior statistician attend open meetings of the DMC; one designated statistician from the coordinating centre prepares reports for, and attends, closed meetings of the DMC. The DMC meets 6–12 monthly, 2–4 weeks before the TSC meets, and provides a report to the chair of the TSC for consideration at that meeting. The DMC charter is available from the corresponding author.

### Adverse event reporting and harms {22}

Given the intensive monitoring of patients with advanced CKD in routine clinical care, the comprehensive data on clinical events recorded directly by the trials unit, and the routine use of pathways that involve preparing for dialysis and preparing for conservative care in the NHS, the study utilises the following risk-adapted safety reporting approach:Serious adverse events are collected as part of the study data on the trial CRFs, including an assessment of expectedness and relatedness by the site.Only SAEs categorised as unexpected and causally related to the intervention require expedited reporting to the CI and sponsor.

Deaths, quality of life and SAEs categorised as unexpected and causally related to the intervention are regularly reviewed by the DMC.

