#### Intervention description {11a}

The intervention arm—‘prepare for responsive management’—is an optimised form of conservative kidney management based on international guidance [5], and developed by UK expert consensus with PPI involvement, and informed by the pre-trial qualitative findings [19]. The difference between the two pathways is that patients randomised to prepare for responsive management have regular support from the kidney unit staff (assessment of their symptoms and advance care planning that includes consideration of priorities for care at home visits and by telephone) and support that responds to their needs (from kidney unit staff, palliative care teams and community staff). They avoid the scans and surgery that normally take place when patients prepare for renal dialysis and therefore any complications of that access surgery. The aim of the pathway is to support patients and respond to their needs in their preferred place of care so that they do not feel they have to swap to dialysis to feel safe and be kept comfortable if/when they develop kidney failure.

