### Assignment of interventions: Blinding

#### Who will be blinded {17a}

Due to the nature of the intervention, participants and those administering the intervention are not blinded to group allocation. Patients are, however, blinded to their randomised allocation prior to completion of their baseline questionnaire to remove bias. Two statisticians are supporting the trial. The senior statistician will remain blinded throughout the trial and be responsible for writing the statistical analysis plan (SAP) and attending TSC meetings. The other trial statistician will perform all disaggregated analyses according to a pre-specified statistical analysis plan and will attend closed Data Monitoring Committee (DMC) meetings, as required. The remaining members of the study team will remain blinded to aggregate data only.

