##### Follow-up assessment and data collection for the RCT

Follow-up data collection for the RCT is summarised in Table 2. Clinical, resource use, laboratory and compliance with the intervention is collected by research nurses from primary and secondary care clinical notes and during study visits/contacts. The physical assessment is performed by the research nurse following standard operating procedures. No blood or urine tests are required other than those that will already have been performed as part of routine care.

**Table 2 Tab2:** Summary of follow up data collection for the RCT

Clinical	Co-morbidities, hospital admissions including dates and causes, dialysis access surgery procedures and complications, other surgery, dialysis treatment received, dietary restrictions, prescribed medication, date, location and cause of death
Resource use	Hospital/nursing home/residential home days/hospice days, other hospital outpatient services and primary care and community services in the last 4 months. Help from family, friends and carers in the last week
Laboratory	Creatinine, urea (pre- and post-dialysis if on haemodialysis), albumin, haemoglobin, haematocrit, mean corpuscular volume, sodium, potassium, bicarbonate, corrected calcium, phosphate, intact parathyroid hormone, total cholesterol. (From the date of the study visit/contact or the closest date prior to the study visit/contact.)
Physical assessment	Weight, blood pressure, heart rate, waist circumference, timed get up and go [30], hand grip strength (Jamar hand dynamometer) [31], WHO performance status
Compliance with trial	Number of home visits by clinical team from kidney unit; Number of attendances at CKD clinic; Number of telephone contacts from clinical team at kidney unit; Number of visits from the palliative care team; Number of telephone contacts from the palliative care team; Advance care agreed; Advance care plan reviewed/updated; Cardiopulmonary resuscitation decision documented; Preferred place of death documented
Patient reported	EQ-5D-5L [25], IPOS-renal [26], ICECAP-O [27], ICECAP-SCM [28], MTBQ [29]
Relative/carer reported	PACKS impact on carers questionnaire [32], QUALYCARE post-bereavement survey [33]

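### The stated DMC review covers deaths, quality of life and SAEs the site calls both unexpected and related, so an imbalance in expected non-fatal harms is not stated to be shown

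*Protocol article*

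**What the plan says.** The section Adverse event reporting and harms {22} describes a risk-adapted approach with three elements.

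- Collection is complete: "Serious adverse events are collected as part of the study data on the trial CRFs", "including an assessment of expectedness and relatedness by the site".
- Expedited reporting to the chief investigator and sponsor is restricted to SAEs that are unexpected and causally related to the intervention.
- For the DMC, "Deaths, quality of life and SAEs categorised as unexpected and causally related to the intervention are regularly reviewed by the DMC".

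Elsewhere, Interim analyses {21b} adds that mortality goes to the DMC by arm. The section on the DMC's composition and role {21a} gives a broader remit: "A DMC monitors accumulating trial data for quality, completeness and patient safety". It also says that a designated statistician prepares the closed reports and that a charter exists. On blinding, "participants and those administering the intervention are not blinded to group allocation" (Who will be blinded {17a}).

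**The concern.** The third element applies to the DMC the same double filter that the second applies to expedited reporting. The two serve different purposes. Expedited reporting looks for single alarming cases, and restricting it to unexpected, related events is ordinary practice in a trial of two routine care pathways. Periodic DMC review looks for a difference between arms in the frequency of events, including events everyone anticipates. In advanced CKD most serious harm is of a known kind, so a filter on expectedness takes out most of what a comparison of the arms would use.

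At stake is whether the committee responsible for patient safety sees a by-arm comparison of non-fatal harm. It may recommend stopping recruitment in all patients or in subgroups (Interim analyses {21b}), and that judgement weighs non-fatal harm as well as death. The filtered counts also depend on judgements made with the arm known, so they may not be comparable between arms.

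**Working it through.** No arithmetic applies, since the article gives no figure on this point. The check sets its sections side by side.

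1. **Which harms does the article itself foresee as differing by pathway?** Intervention description {11a} says of responsive-management participants: "They avoid the scans and surgery that normally take place when patients prepare for renal dialysis and therefore any complications of that access surgery". The description of the responsive management pathway lists unplanned attendances for fluid overload, and for infection causing systemic illness, among the triggers for senior review. Both kinds of event are anticipated in the document, so a site would usually class a serious instance as expected.

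2. **Do they pass the stated filter?** The DMC sentence requires an SAE to be unexpected and causally related. An event classed as expected fails the first condition whatever its cause, and so falls outside the SAEs named for regular review.

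3. **Does the relatedness condition treat the arms alike?** The article's headings call responsive management the intervention and dialysis preparation the comparator. Other places use the word for both arms: Criteria for discontinuing or modifying allocated interventions {11b}, Implementation {16c} and Resource-use data collection. The term is therefore ambiguous. A complication of dialysis preparation might or might not be counted as related, depending on how a site reads it.

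4. **Is the classification made with the arm known?** The blinding section refers to participants and those giving the intervention and does not name the SAE assessor. However, site staff operate the randomisation system (Implementation {16c}), the research nurse tells responsive-management participants what will follow after allocation, and research nurses record the care delivered in both arms (Strategies to improve adherence to interventions {11c}). The site's assessment is thus made where the allocation is known.

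5. **Are the unfiltered data available?** Yes. All SAEs are on the case report forms, and the follow-up data table includes "hospital admissions including dates and causes, dialysis access surgery procedures and complications". The narrowing lies in what is listed for review, not in what is collected.

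6. **Do the other two review streams fill the gap?** In part. Mortality by arm shows fatal harm. Quality of life is measured every 4 months, by proxy where the patient is too unwell. It may register the burden of non-fatal harm, but it does not identify the cause or count the events.

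**The case against.** The strongest reply is that the sentence is not exclusive. In that section, 'only' governs expedited reporting. The DMC sentence says what is regularly reviewed, not that nothing else is. The remit in {21a} is wide, and table lists for closed reports normally sit in a charter, which exists but is not shown. This stands. A reader might infer that the DMC cannot see expected harms, or that it reviews SAEs and nothing else. The documents support neither: deaths and quality of life are in the same sentence, and the charter may ask for more.

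A reader might also infer that comparator harms are excluded by the word 'intervention'. Given the mixed usage, they are only not clearly included.

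It is also fair to say that more access complications under dialysis preparation are built into the comparison and are not in themselves an emergent signal. Their frequency and severity still matter to a safety committee, and the same reasoning does not cover overload or infection admissions. Hospital-free days is a secondary outcome, but the article does not list it for DMC review.

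It is tempting to put a count on the SAEs left out. Any such figure would need an SAE rate and a share classed as unexpected and related, neither of which the article gives, and it would have to exclude time after death.

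Finally, the change comes late. Recruitment was due to finish at the end of August 2024 and follow-up at the end of August 2025. With meetings every 6 to 12 months, those 12 months hold about one (12/12) or two (12/6) meetings. That limits the benefit but does not remove it.

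**Conclusion.** The point holds in a limited form. The article does not leave the DMC's regular content wholly open. It names three streams, and the SAE stream is confined to events that the site, knowing the allocation, classes as both unexpected and related to an ambiguously defined intervention. Followed as written, an imbalance in expected non-fatal harms is not stated to be shown to the DMC, and could go unseen or appear only indirectly through quality of life. The stated grounds for a risk-adapted approach support limiting expedited reports. They give no reason to limit aggregate by-arm tables of data already collected.

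The size is qualitative: a gap in the stated scope of safety review, with no effect on the primary analysis. The conclusion assumes that sites would usually class harms the protocol foresees as expected, and that the unseen charter does not already call for the fuller tables. If it does, what remains is a sentence to correct. This should be changed because it bears on patient safety and the remedy is cheap.

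**What to change.** Leave expedited reporting unchanged. In Adverse event reporting and harms {22}, state that each closed DMC report tabulates all SAEs by arm and by category, regardless of expectedness or relatedness. The table should give the number of events, the number of participants with at least one, and the rate per person-year alive. Time alive is the right denominator because participants stay in the primary outcome after death with a utility of 0, when no SAE can occur. Add hospital admissions by cause and dialysis-access complications, both already on the follow-up case report form. Define relatedness as related to either allocated pathway. If the DMC charter already requires these tables, correct the sentence to say so.

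The cost is a slightly longer closed report, prepared by the statistician who already produces it. No new data collection is needed.
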